### Participants

All patient with an elective cardiac catheterization, hospitalized in the Ernst-von-Bergmann clinic in Potsdam or Bad Belzig, and all staff members at catheterization lab at the Ernst-von-Bergmann clinic in Potsdam are eligible for participation. Patients between the ages of 30 and 75 years with a scheduled heart catheter examination were recruited for study participation. The following criteria should be met: the CC examination have to be elective and non-acute. In addition, only patients, scheduled for coronary angiography, are included. Exclusion criteria were: the inability to fill in a questionnaire, pregnancy and mental health problems. Only practitioners—physicians or nurses—that work at the catheterization lab are included in the intervention trail. The exclusion criterion for practitioners is the presence of an endocrinological metabolic disease. All participants have to sign informed consent after receiving written and verbal information. The study is conducted according to the Declaration of Helsinki (ethics approval 03/06/2021, ethics review board University of Potsdam No. 38/2021) and complied with the Consolidated Standards of Reporting Trials (CONSORT).

### Sample Size Determination

We calculated the sample size for two patient groups for two measurement points based on a pilot study. The sample was powered to assume a medium effect size (*d* = 0.25) and a minimum detectable clinical difference of 0.5 standard deviation on the (z-standardized) main criterion: perceived stress. For the main criterion, the power for significant group differences is 1-β = 0.93 with a case number of *N* = 60 people per group (38). As the sample for the practitioners was limited to all members of the catheterization lab of the clinic who fulfill the inclusion criteria, a sample size determination was not required.

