## Methods and Analysis

### Study Design

The multicenter study “Heartbeat” implement a randomized and controlled pre-post-study design involving two intervention trials with parallel groups, for patients with elective cardiac catheterization and practitioners at the catheterization lab, respectively (Figure 1, DRKS No: 00026624^1^). The patient study with a 1:1 randomization by person and a standard treatment control group involves three measurement points: the day before (M1 = admission day) and the day after the video-based stress management intervention and cardiac catheterization examination (M2 = CC examination day), and 6 months after baseline (M3). The MBSR intervention trail for the practitioners at the CC lab involves a 1:1 randomization by group and a no-treatment control group with three measurement points: before (M1) and after the 8-week (M3) intervention with a mindfulness-based stress reduction program, as well as 6 months after baseline (M3). The study takes place at the two clinic sites of the Ernst-von Bergmann community clinic, in Potsdam (patients and practitioners) and Bad Belzig (only patients). The time of data collection is estimated with ~1 h for all questionnaires and 2 days for the physiological measurements (practitioners). The data collection period is planned from 01/2021 to 12/2022.

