### Statistical Analysis

All statistical analyses will be performed using SPSS. The data of the practitioners will be mainly analyzed descriptively due to the small sample size. Interferential statistics will be used to identify group differences. A comparison with norms of the German general population will be performed to assess the stress of the practitioners in the cardiac catheter laboratory. Baseline and post-interventional physiological data like circadian profile slopes of HRV and derived indicators (SDNN, RMSSD, number and percentage of R-R intervals lower or >50 msec) as well as saliva cortisol, alpha-amylase and lysozyme measurements will be compared on an intraindividual level. The data of the patients will be analyzed according to a multivariate variance analysis (between-subject factor: intervention group vs. control group). Sociodemographic data, sedative medication, adherence to the intervention will be implemented as control variables or stratification variables for subgroup analysis. Statistical significance is set at *p* < 0.05 (two-sided) and effect sizes will be reported.

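### Sample size: two conflicting effect sizes are given for perceived stress, and the power of 0.93 with 60 patients per group cannot be reproduced from the stated inputs

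*Protocol article*

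**What the plan says.** All the figures are in the Sample Size Determination section of the protocol article.

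- Design of the calculation: "We calculated the sample size for two patient groups for two measurement points based on a pilot study".
- First effect size: "The sample was powered to assume a medium effect size (*d* = 0.25").
- Second effect size, in the same sentence: "a minimum detectable clinical difference of 0.5 standard deviation on the (z-standardized) main criterion: perceived stress".
- Result: "the power for significant group differences is 1-β = 0.93 with a case number of *N* = 60 people per group".

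The section names no test, significance level or correlation between the two measurement points. The Statistical Analysis section supplies the level, "Statistical significance is set at *p* < 0.05 (two-sided"), and describes the patient analysis as a "multivariate variance analysis (between-subject factor: intervention group vs. control group"). It lists sociodemographic data, sedative medication and adherence as control or stratification variables. It mentions neither a time factor nor adjustment for baseline perceived stress. Study Design gives 1:1 allocation of individual patients. Table 1 schedules the PSS-10 for patients at M1 (the day before catheterization) and M3 (six months after M1), and not at M2.

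**The concern.** For a z-standardised outcome the SD is 1, so d is the group difference in SD units. A d of 0.25 and a difference of 0.5 SD therefore cannot both be the target for the same criterion. The reader cannot tell which one the 0.93 refers to, and the simplest calculation returns 0.93 for neither.

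This affects how the result will be read. Power of 0.93 tells the reader that the trial has a 7% chance of missing its target effect, and a null result on perceived stress would be judged against that figure. If the real power is lower, or refers to a different effect, a null result would be given more weight than it can bear.

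**Working it through.** **Inputs.** From Sample Size Determination: n = 60 per group, difference 0.5 SD or d = 0.25, SD = 1, two measurement points, stated power 0.93. From Statistical Analysis: two-sided alpha 0.05. From Study Design: 1:1 allocation. The correlation r between the two points is not stated and is varied below. All 60 per group are taken as analysed until step 5.

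**1. Two groups, one time point.** The noncentrality is d × √(n/2) = d × √30, with 118 degrees of freedom (noncentral t).

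| Effect | Noncentrality | Power, 60 per group | n per group for 0.93 |
|---|---|---|---|
| 0.5 SD | 2.739 | 0.775 | 96 |
| d = 0.25 | 1.369 | 0.274 | 379 |

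The normal approximation gives 0.782 and 0.277, and 95 and 378 per group. A one-sided test, which the article does not plan, gives 0.860 and 0.388. The difference detectable with power 0.93 at 60 per group is 0.63 SD. None of these calculations returns the stated figure.

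**2. What would return 0.93, using the two measurement points?** Each route needs a standardised effect of about 0.632 after allowing for the correlation.

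| Model | Effective effect | Correlation giving 0.93 |
|---|---|---|
| ANCOVA on M1, 0.5 SD | 0.5/√(1 − r²) | about 0.61 |
| Change score, 0.5 SD | 0.5/√(2(1 − r)) | about 0.69 |
| Between-groups repeated measures, f = 0.25 | see step 3 | 0.25 |
| ANCOVA or change score, d = 0.25 taken literally | as above, with 0.25 | about 0.92 |

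**3. The repeated-measures route.** For two equal groups f = d/2, so f = 0.25 is the same effect as 0.5 SD. With N = 120, m = 2 and r = 0.25, the noncentrality is f² × N × m/(1 + (m − 1)r) = 0.0625 × 240/1.25 = 12. On 1 and 118 degrees of freedom this gives power 0.930, which matches the stated figure exactly. It also makes the two effect sizes agree if the d was meant as an f.

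This test compares the groups on the average of the two points and assumes a difference of 0.5 SD at both. Perceived stress is measured only at M1 and M3, and M1 precedes the intervention, so randomisation makes the expected M1 difference zero. The average difference is then 0.25 SD, the noncentrality falls to 12/4 = 3, and power is 0.40.

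**4. Models suited to a baseline and one follow-up, 0.5 SD, 60 per group.**

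- Unadjusted M3 comparison: 0.78.
- ANCOVA on M1 with r = 0.5: effective effect 0.5/√0.75 = 0.577, power 0.88.
- ANCOVA with r = 0.6: power 0.92.

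**5. Loss before M3.** The article gives no return rate. With an assumed 20% loss, 60 × 0.8 = 48 per group remain, and power at 0.5 SD is 0.68 unadjusted or 0.80 by ANCOVA at r = 0.5.

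**The case against.** The strongest reply is that 0.93 has not been shown to be wrong. The article says that the calculation used two measurement points, and the 0.78 ignores that input. The value 0.25, called medium and set beside 0.5 SD, looks like an f printed as a d; on that reading there is one effect, and 0.93 follows from it under a repeated-measures model. ANCOVA and change-score analyses also reach 0.93 at 0.5 SD, and neither assumes a baseline difference. The analysis section names the between-subject factor without excluding a time factor or baseline adjustment. The test, the correlation and the allowance for loss are details that an article may leave to a fuller document.

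Most of this stands, and it limits the point. A reader might infer that the true power is 0.78, or even 0.27, or that the risk of missing the target effect is at least 22%. The documents do not support that: 0.78 belongs to an unadjusted one-time-point comparison that the article never names, and ANCOVA at plausible correlations does better. A reader might also infer that the authors assumed a difference at baseline. That is only a guess from the exact match in step 3, because the correlation of 0.25 was chosen to return 0.93.

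The reply does not remove the contradiction in the printed effect sizes. That is an error in what the article states and cannot be excused as omitted detail. Nor can 0.93 be checked while the effect it refers to is ambiguous and every route to it rests on an unstated model and correlation.

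**Conclusion.** The point holds as follows: the effect size is stated in two conflicting ways, and the power of 0.93 cannot be reproduced from the stated inputs. The simple two-sided comparison gives 0.78 at 0.5 SD and 0.27 at d = 0.25.

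At 0.5 SD, 0.93 is attainable with an M1–M3 correlation of about 0.61 (ANCOVA) or 0.69 (change score). The article gives no evidence for either value. The calculation that matches most closely, repeated measures with f = 0.25 and correlation 0.25, would be unsuitable here, because its power is about 0.40 when the effect is absent at M1. That this was the source is an inference.

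The 0.78 and 0.88 (ANCOVA at an assumed correlation of 0.5) assume complete M3 data; the figures after loss rest on an assumed 20%.

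**What to change.** Rewrite the sample-size paragraph.

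1. State one target effect, 0.5 SD on perceived stress. Relabel the 0.25 as f or delete it.
2. Name the test, the significance level and the M1–M3 correlation, and restate the power for the M3 group comparison that will be run: 0.78 if unadjusted, or 0.88 for ANCOVA on M1 PSS at an assumed correlation of 0.5.
3. Keep 0.93 only if the analysis is ANCOVA and the pilot (50 participants, according to Study Status) supports a correlation of about 0.61.
4. Give the figure at the expected number of M3 returns. With an assumed 20% loss it is 0.68 unadjusted or 0.80 by ANCOVA at 0.5.

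The cost is one corrected paragraph and possibly a less favourable stated power. No extra patients are needed.

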### Recruitment, Screening and Informed Consent

The recruitment of the participants for both the patients and practitioners take place directly on site in the clinic by a research assistant of the study. Patients will be consecutively asked to participate on the day they arrive at the clinic, preconditioned they fulfill all inclusion criteria proofed by doctors. All practitioners of the catheterization lab from the Ernst-von-Bergman clinic are eligible for the study and will be recruited by the study personnel. All patients and practitioners will provide written, informed consent after a comprehensive information about the aim and the procedures the of study in written and verbal form. All participants will be additionally informed about their right to refuse to participate or to withdraw consent to participate at any time of the study (before anonymization of data) without reprisal.

### Randomization Procedure and Blinding

The process of randomization to the allocation arm was performed prior to recruitment via a randomization list. This randomization list was generated via the computerized randomization tool Research Randomizer (https://www.randomizer.org/). Participants will be randomly assigned to either the intervention or control condition according to the randomization list. Patients and practitioners cannot be blinded due to their active role in the intervention. Practitioners at the cardiac catheterization laboratory are blinded to the group allocation of the patients.

### Experimental Procedure/Intervention

As both patients with an elective cardiac catheterization (CC) examination and practitioners at the catheterization lab face different stressors, both groups received different interventions for stress management.

The CC for the included study participants is elective (non-acute) and medically recommended to evaluate or confirm coronary artery disease, congenital heart disease, heart failure, heart valve disease or aorta dysfunction, heart muscle function and to decide for further treatment. On the admission day (M1), all patients get the usual medical patient information from a cardiologist and anesthetist and get prepared for the examination (fasting, no smoking, evaluation of medication). All patients that fulfill the inclusion criteria concerning age and CC examination will be randomly dedicated to intervention group and control group and subsequently contacted by a research assistant who present the study and its aims and answer all questions. All participants have to sign informed consent after receiving written and verbal information. Afterwards all participants receive the questionnaires for M1 (pre-intervention questionnaire) and only patients in the intervention group get and only patients in the interventions group get the intervention (see The intervention for patients). The next day (M2), all patients get the CC examination at the catheterization lab. During the CC the patient is usually awake and conscious as the hostipal policy is not to administer any tranquilizer, sedatives and anxiolytics as a routine before or during CC procedure. However, patients get sedatives if needed and the type of sedative and dose is documented in a questionnaire by physicians or nurses of the CC lab. After disinfection and local anesthetization of the insertion site (groin, wrist or rarely crook of the arm), the catheter is inserted through a plastic introducer sheath. The catheter is guided through the blood vessel to the coronary arteries and coronary angiography is done by injecting a contrast dye that is visible in X-ray images. The following further diagnostic and interventional procedures can be performed during a cardiac catheterization: myocardial biopsy, levocardiography, right ventriculogram, coronary angiogram, and treatments for narrowing or blockages in the blood vessels like balloon dilatation and stent placement. The aftertreatment includes a bed rest for several hours in the ward until the following day of discharge. The participants fill in the post-intervention questionnaire during the bed rest/stay in the ward (M2).

*The intervention for patients* focusses on a video-based standardized patient information about the cardiac catheterization examination and further involves a short patient education with different stress management technics. The video-based standardized patient information gives information about the aim and general process of the CC, like location and aftercare of the puncture, position of the participants during the examination how the procedure is monitored. Further information comprises potential but rare complications and side effects like additional interventions, circulatory disruptions, cardiac arrhythmia, bleedings and (temporary) pain. The second part of the video broaches the issue of stress management technics to handle anxiety, tension and malaise. It provides brief instructions for relaxation, meditation and guided imagery techniques as well as cognitive distraction tasks, and cognitive reframing. All cognitive techniques are easy to apply after one presentation and involve methods to stop negative thoughts, distract from unhelpful thought patterns, to guide attention and positive expectations, to lower tension and support relaxation. For example, the patient should recite the alphabet and imagine a positive thing or event for every letter that he/her would be able to do after the CC. The patient should guide his/her attention to their most pleasant vacation and reactivate the feelings and thoughts present at that time. If a patient feels discomfort or pain, he/she should guide his attention to his/her big toe or left hand for cognitive distraction. The video encourages the patient to speak to the doctors and nurses about complaints and needed assistance. The video is shown to the patients the day before the CC via a tablet bedside in the clinic and is complementary to the non-standardized patient education by the medical doctor that is clinical routine for both intervention and control group.

*The intervention for practitioners* includes an 8-week Mindfulness-based stress reduction (MBSR) program based on the Jon Kabat-Zinn method (39, 40), which take place weekly for 1.5 h. For the first 6 weeks, the intervention is supervised by an experienced MBSR practitioner directly at the clinic site. The following 2 weeks, it takes place at home guided by an audio guide and an exercise book. The MBSR program includes body scan, sitting meditation and Hatha-yoga exercises, as well as breathing exercises throughout all three types of meditation. During the body scan every part of the body is systematically and conscious sensed in a lying position to enhance mindfulness. Key component of the sitting meditation is the upright position and conscious focus on breathing and staying in a mindful state. The different yoga poses (asanas) comprise balance and stretching elements for lying and upright positions. The exercise within MBSR differs from week to week with regard to the yoga elements, but every single routine starts with body scan and sitting meditation.

Additionally, an operative guideline for interaction with colleagues, conduct during and after complications and traumatic events during a cardiac catheterization examination was developed on basis qualitative interviews with staff members of the catheterization lab prior to the study. These guidelines for mindful and self-aware behaviors are printed and hang out as a poster at the catheterization lab.

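### Patients are assigned to an arm before the study is explained and consent is sought, with no stated concealment from the recruiter, so consent can depend on the arm

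*Protocol article*

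**What the plan says.** The order of events for patients is in the protocol article, Experimental Procedure/Intervention. Patients who meet the age and examination criteria "will be randomly dedicated to intervention group and control group and subsequently contacted by a research assistant who present the study and its aims". The next steps are consent ("All participants have to sign informed consent after receiving written and verbal information") and then baseline: "Afterwards all participants receive the questionnaires for M1 (pre-intervention questionnaire"). Only after that does the intervention group see the video.

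Randomization Procedure and Blinding points the same way: "The process of randomization to the allocation arm was performed prior to recruitment via a randomization list". On blinding, it says "Patients and practitioners cannot be blinded due to their active role in the intervention" and "Practitioners at the cardiac catheterization laboratory are blinded to the group allocation of the patients". The recruiter is not mentioned there.

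Recruitment, Screening and Informed Consent says that recruitment will "take place directly on site in the clinic by a research assistant of the study", and that "Patients will be consecutively asked to participate on the day they arrive at the clinic". Strategies to Improve Adherence to Interventions also puts the baseline questionnaire after recruitment, study education and consent.

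**The concern.** Preparing a randomisation list before recruitment is ordinary practice. The difficulty is that the individual patient is placed in an arm before the study has been explained to that patient. The person who then explains it is a research assistant for whom no blinding or concealment is stated.

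Two things can then vary with the arm: how the study is presented, and whether the patient agrees. Stress and anxiety plausibly influence whether someone agrees to watch a video about the procedure the day before it. Perceived stress, mood and tension are among the primary outcomes for patients. A patient who refuses after assignment leaves no data, so the analysed groups are those who consented within each arm and no longer the groups that chance formed.

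There is a second, conditional risk. M1 is self-reported and comes after assignment. If the explanation of the study tells patients their arm, the M1 answers could reflect that knowledge.

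**Working it through.** **Order of events, from the text**

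1. Eligibility is established, then the arm is assigned.
2. The research assistant contacts the patient and presents the study.
3. The patient consents or refuses.
4. M1 questionnaire.
5. Video, intervention arm only.

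Steps 2 to 4 all follow assignment. Two sections agree on this, so it is a stated rule and not a detail left out for brevity.

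**Size.** The plan gives no figure for this point, so there is none to reproduce. Its power statement does not enter. Inputs from the plan are 60 patients per group, a 0.5 SD target difference (Sample Size Determination) and a two-sided 5% level (Statistical Analysis). Consent rates and their dependence on stress are not in the plan; the values below are assumptions.

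*Graded consent.* Let baseline stress be x ~ N(0,1). Control patients consent regardless of x. In the intervention arm, logit p(x) = logit(p0) + ln(OR)·x, where p0 is the consent probability at average stress. The mean among those who consent is E[p(x)·x] / E[p(x)], and this is the baseline difference between arms. An odds ratio below 1 gives the mirror image.

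For the type I error of an unadjusted comparison, SE = √(2/60) = 0.183 SD, and error = Φ(−1.96 + shift/SE) + Φ(−1.96 − shift/SE).

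| p0 | OR per SD | Shift (SD) | Type I error |
|---|---|---|---|
| 60% | 1.25 | 0.089 | 0.078 |
| 60% | 1.5 | 0.159 | 0.140 |
| 60% | 2.0 | 0.257 | 0.292 |
| 80% | 1.25 | 0.046 | 0.057 |
| 80% | 1.5 | 0.083 | 0.074 |
| 80% | 2.0 | 0.143 | 0.122 |
| 90% | 1.25 | 0.024 | 0.052 |
| 90% | 1.5 | 0.043 | 0.056 |
| 90% | 2.0 | 0.078 | 0.071 |

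These error rates take the baseline shift to carry over in full to the outcome. If only half of a 0.20 SD shift did so (0.10 SD), the error would be 0.085 rather than 0.195.

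*Near worst case.* If the most stressed fraction q all refuse in one arm and nobody refuses for that reason in the other, the mean shift is φ(z)/(1−q), where z is the upper-q point of the standard normal:

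- q = 5%: 0.11 SD, or 22% of 0.5 SD
- q = 10%: 0.19 SD, or 39%
- q = 20%: 0.35 SD, or 70%

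**The case against.** The strongest reply is that only the order of events is documented, and that harm from it is inferred. Much of this stands, and it rules out several stronger readings that a reader might draw.

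- *That the assistant knows the arm.* No section says that the assistant holds or sees the list, and a journal article may leave custody of the list to the full protocol. The text supports only that the assistant could know.
- *That patients are approached selectively.* Patients are to be asked consecutively and their inclusion criteria are checked by doctors. This limits selective approaching. It does not govern how the study is presented or who consents.
- *That the M1 baseline is contaminated.* Nothing says that patients have learned their arm when they fill in M1. The lack of blinding is attributed to their active role in the intervention, which begins with the video, and M1 is labelled as preceding the intervention. Contamination is possible, not established.
- *That adjusting for M1 cannot repair the problem.* This holds only if M1 has itself been shifted by knowledge of the arm. If it has not, adjustment would remove much of an imbalance in baseline stress, because that is what M1 measures.
- *That a shift of 0.11 to 0.35 SD is to be expected.* Those figures need sharp refusal in one arm only. The intervention is a 10-minute bedside video and the control is usual care, so the difference in burden is small. The low end of the graded model is negligible.

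The sentence might also be loose drafting about a list prepared in advance. Even so, two sections give the same order, and anyone following the text would assign first and ask afterwards. What remains is that the written order allows differential consent and loses post-assignment refusals from the comparison.

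**Conclusion.** The point holds in this form: as written, the plan assigns each eligible patient before approach, consent and M1, and states no concealment from the recruiter, so presentation and consent can depend on the arm. It should be corrected, because it bears on the randomisation itself and the correction is cheap.

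The size of any bias is unknown. Under the assumed graded consent it runs from about 0.02 SD with type I error 0.052, which is negligible, to about 0.26 SD with type I error 0.29, which is serious with 60 per group. Those error rates apply to an unadjusted comparison with full carry-over of the shift. The range of 0.11 to 0.35 SD is a near worst case. Any effect on M1 depends on whether patients are told their arm during the explanation, which the article does not say.

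**What to change.** Keep the pre-generated list. Rewrite the patient sequence in Randomization Procedure and Blinding and in Experimental Procedure/Intervention so that it reads: eligibility; information and consent; M1 questionnaire; reveal of the next assignment from sequentially numbered, opaque, sealed envelopes; then the video for those assigned to it.

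Study Status says that the first participants have already been recruited. For patients enrolled under the order now written, report the numbers approached, refused and consented by arm. Refusals can be attributed to an arm because assignment came first. Add a sensitivity analysis that leaves these patients out. If practice on the ward already follows the proposed order, only the wording needs to change.

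The cost is preparing the envelopes and a small amount of extra reporting. No visit is added and the planned sample size does not change.
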